### Outcome measures

Several instruments will be used to assess the effects of brief sex counselling on sexual functioning, depression and other psychological and physical complaints, and on secondary outcomes. Furthermore instruments will be used to assess the cost-effectiveness of brief sex counselling from a social perspective. The outcomes will be measured before randomization (during initial screening), at baseline and at 3, 6, 9 and 12 months after baseline (Additional file 1).

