### Randomisation and procedure

For this study a block randomisation procedure will be used to ascertain that each intervention runs in equally large groups. Although the order of the interventions varies randomly within each block, a person running the trial could deduce some of the next treatment allocations if they discovered the block size. In this study we use larger block sizes (30) and randomly vary in block size which can ameliorate this problem [55]. Allocation will be performed by a central independent research assistant after getting informed consent, screening, and checking the in- and exclusion criteria, using Schouten's (1995) adaptive biased urn randomization for small strata. This keeps randomization unpredictable up to and including the last participant on each site, while keeping the group sizes at each site in good balance [56].

The questionnaires will be administered using a computer. All assessments will take place at home via internet. Preceding an upcoming assessment point, participants will receive an email (one week before the end of the treatment and 3 months after the start of the follow-up measurement). If a participant fails to complete the assessment within one week, an email-reminder will be sent. When the participant fails to fill in the questionnaires, a phone call will be made.

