### Analyses

#### Clinical analyses

Our primary (base-case) analyses will be performed according to the intention-to-treat principle, including data from all participants regardless of whether they received the intervention or not. For the analyses we will use SPSS statistical software and Excel (for the bootstraps). Respondents for whom at least 75% of the data per measurement instrument are available will be included in the analysis. Missing data on item level will be handled using SPSS missing value analysis. Completely missing measurements will be handled using multiple imputation. Analysis will include comparisons of the intervention groups (brief sex counselling, sexological treatment and waiting list) as well as more complicated multi-level analysis. The accuracy of the findings will be expressed in terms of 95% confidence intervals.

To test the main research questions, difference scores for all outcome variables will be calculated and compared between the three intervention groups using MANOVA. In the case of significant multivariate results, subsequent univariate analysis using independent groups t-tests will be conducted to assess the significance of differences pre/post intervention between control and experimental groups.

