#### Economic evaluation

A baseline analysis will be performed to examine the comparability of groups at baseline for both costs and outcomes. If necessary methods will be applied to control for differences in baseline [57]. To investigate whether data are normally distributed a Kolmogorov-Smirnov test will be performed. Despite the usual skewness in the distribution of costs, the arithmetic means will be generally considered the most appropriate measures to describe cost data [58,59]. Therefore arithmetic means (and standard deviations) will be presented. In case of skewness of the cost data, non-parametric bootstrapping will be used to test for statistical differences in costs between the intervention and control group. The bootstrap replications will be used to calculate 95% confidence intervals around the costs (95% CI), based on the 2.5^th ^and 97.5^th ^percentiles. If cost data are distributed normally, t-tests will be used.

The incremental cost-effectiveness ratio (ICER) will be determined on the basis of incremental costs and effects of sex counselling compared to sexological treatment and a waiting-list group. The cost-effectiveness ratio will be stated in terms of costs per outcome rate (increase in sexual functioning, decrease of depressive symptoms) the cost-utility ratio will focus on the net cost per utility gained.

The robustness of the ICER will be checked by non-parametric bootstrapping. Bootstrap simulations will also be conducted in order to quantify the uncertainty around the ICER, yielding information about the joint distribution of cost and effect differences. The bootstrapped cost-effectiveness ratios will be subsequently plotted in a cost-effectiveness plane. The choice of treatment depends on the maximum amount of money that society is prepared to pay for a gain in effectiveness, which is called the ceiling ratio. Therefore, the bootstrapped ICERs will also be depicted in a cost-effectiveness acceptability curve showing the probability that sex counselling is cost-effective using a range of ceiling ratios. Additionally, to demonstrate the robustness of our base-case findings, multi-way sensitivity analyses will be performed [60].

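### The main clinical test uses difference scores with no baseline covariate; this is valid but can cost precision that baseline-adjusted analysis would recover

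*Protocol article*

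**What the plan says.** Under Clinical analyses, the test of the main research questions is that "difference scores for all outcome variables will be calculated and compared between the three intervention groups using MANOVA". If the multivariate result is significant, independent-groups t-tests follow "to assess the significance of differences pre/post intervention between control and experimental groups". No covariate is named for either step, and an independent-groups t-test cannot carry one.

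Three other statements bear on this:

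- The preceding paragraph of the same section says the analysis will include comparisons of the groups "as well as more complicated multi-level analysis". Its levels, covariates and role are not given, and the main questions are assigned to the difference-score tests.
- The only mention of baseline adjustment is in the Economic evaluation part of the Analyses section, and it is conditional: "If necessary methods will be applied to control for differences in baseline".
- The data needed are collected. Outcome measures states: "The outcomes will be measured before randomization (during initial screening), at baseline and at 3, 6, 9 and 12 months after baseline". Randomisation and procedure describes an allocation aimed at "keeping the group sizes at each site in good balance".

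**The concern.** Subtracting baseline from follow-up assumes that each extra point at baseline carries through as a full point at follow-up. If the true slope is below 1, subtraction over-corrects and leaves baseline noise in the outcome. Estimating the slope removes that noise.

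Participants enter by scoring beyond a cut-off on the QSSD and the IIEF or FSFI (Recruitment), which are also the sexual-functioning outcomes. Some regression to the mean is therefore expected, which is one reason to doubt a slope of exactly 1.

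What is at stake is the width of the confidence intervals and the power obtained from the same participants. The validity of the comparison is not in question.

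**Working it through.** **Inputs.** From Sample size: 95 per group, target d = 0.40, two-sided alpha 0.05, 150 recruited per condition. Assumed, because the article does not give them: the baseline-to-follow-up correlation rho (0.3, 0.5, 0.7) and q, the baseline SD divided by the follow-up SD. The effect d is expressed on the follow-up SD, set to 1.

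**The plan's own figure.** Sample size claims 95% power with 95 per group for an effect size of 0.41, by repeated-measures MANOVA. Read as a two-group comparison of a single score, exact noncentral t gives 80.3%. Read as a change-score comparison, 95% is reached only with rho of about 0.69 to 0.70. The article states neither the correlation nor the number of measurements, so the figure cannot be reproduced from what is given. It therefore does not settle rho for the check below.

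**Variance per participant.**

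- Change score: 1 + q² − 2·rho·q, which is 2(1 − rho) when q = 1.
- Baseline-adjusted (ANCOVA): 1 − rho².
- Ratio: (1 − rho²)/(1 + q² − 2·rho·q), which is (1 + rho)/2 when q = 1.

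The slope of follow-up on baseline is rho/q. The two methods are equally precise only when this equals 1.

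**Power.** SE = √(2 × variance/n), with noncentrality 0.40/SE. Example at rho = 0.5, q = 1, n = 95:

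- Change score: SE = √(2 × 1.00/95) = 0.145; 0.40/0.145 = 2.76; power 78.3%.
- Adjusted: SE = √(2 × 0.75/95) = 0.126; 0.40/0.126 = 3.18; power 88.6%.

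**Equal SDs (q = 1).**

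| rho | Change variance | Adjusted variance | Ratio | SE reduction | Power, n = 95 | Power, n = 150 |
|---|---|---|---|---|---|---|
| 0.3 | 1.40 | 0.91 | 0.65 | 19.4% | 64% to 82% | 83% to 95% |
| 0.5 | 1.00 | 0.75 | 0.75 | 13.4% | 78% to 89% | 93% to 98% |
| 0.7 | 0.60 | 0.51 | 0.85 | 7.8% | 94% to 97% | 99.4% to 99.8% |

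A simulation of 4,000 trials per rho at 95 per arm gave variance ratios of 0.65, 0.76 and 0.85, in line with the formula.

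**Baseline SD narrowed by the cut-off (q = 0.7).**

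| rho | Change variance | Adjusted variance | Ratio | Power, n = 95 |
|---|---|---|---|---|
| 0.3 | 1.07 | 0.91 | 0.85 | 76% to 82% |
| 0.5 | 0.79 | 0.75 | 0.95 | 87% to 89% |
| 0.7 | 0.51 | 0.51 | 1.00 | 97% to 97% |

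In the last row the slope is 0.7/0.7 = 1, so nothing is gained. At q = 0.85 the ratios are 0.75, 0.86 and 0.96.

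**Site.** If 1% to 10% of the change-score variance lies between sites (assumed), leaving site out inflates the SE by about 0.5% to 5.4%.

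**The case against.** The strongest reply has four parts.

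1. *The size is unknown and may be small.* This stands. The larger figures need a low rho and equal SDs. The cut-off that makes regression to the mean likely may also narrow the baseline SD, which shrinks the gain. At the 150 recruited per arm, the power differences are also smaller than at 95.

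2. *The multi-level analysis may already adjust for baseline.* It may, and a condensed article need not list its covariates. But the article does state which test answers the main questions, and it is the difference-score one.

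3. *Difference scores already use baseline, and randomisation protects them.* Correct. A reader might infer that selection by cut-off, or a chance baseline imbalance, biases the contrast. The article does not support that: regression to the mean acts alike in all randomised arms. A chance baseline difference enters the contrast multiplied by (slope − 1), which averages to zero over randomisations. The loss is of precision.

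4. *The text does not say that visits are dropped or that site matters much.* A reader might infer from the pre/post wording that the intermediate visits are discarded. The article does not say how many visits the difference scores cover, and its Sample size section is built on repeated-measures MANOVA. On site, stable additive differences cancel in a change score, so the expected gain is small.

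A simple pooled model would also not be free of difficulty. The FSFI is for women and the IIEF for men, and a sex covariate does not put them on one scale.

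**Conclusion.** The point holds as one of efficiency. The article fixes a main test that is valid and unbiased under randomisation. In large samples that test is at best as precise as the baseline-adjusted version, and it is less precise whenever the slope of follow-up on baseline differs from 1.

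Across rho 0.3 to 0.7, the variance ratio runs from 0.65 to 0.85 with equal SDs and from 0.85 to 1.00 with a baseline SD of 0.7 times the follow-up SD. Power gains at 95 per arm therefore range from about 18 percentage points (64% to 82%) to none. All of these figures rest on assumed values of rho and q. The case for changing rests on the fact that adjustment costs almost nothing and, apart from one degree of freedom, does not lose precision.

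**What to change.** In Clinical analyses, replace the difference-score comparison, for each outcome, by the follow-up score adjusted for its own baseline score. MANCOVA followed by ANCOVA is the simple version; a mixed model over the visits with baseline as a covariate is the fuller one. In addition:

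- Keep the planned multivariate gate before the univariate comparisons, so that multiplicity control is not weakened.
- Analyse the FSFI and IIEF within sex, or on a standardised scale, before any pooling.
- Include site, because allocation is balanced by site, with little gain expected.
- Read the brief-versus-delayed contrast no later than the end of the 26-week waiting period, after which the delayed group may choose either treatment (Delayed treatment section).
- Say how the multi-level analysis relates to this main test.

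No new data are needed, and SPSS, already named, fits these models. The cost is slight extra analysis work, mainly in handling the sex-specific scales.

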#### Economic evaluation

A baseline analysis will be performed to examine the comparability of groups at baseline for both costs and outcomes. If necessary methods will be applied to control for differences in baseline [57]. To investigate whether data are normally distributed a Kolmogorov-Smirnov test will be performed. Despite the usual skewness in the distribution of costs, the arithmetic means will be generally considered the most appropriate measures to describe cost data [58,59]. Therefore arithmetic means (and standard deviations) will be presented. In case of skewness of the cost data, non-parametric bootstrapping will be used to test for statistical differences in costs between the intervention and control group. The bootstrap replications will be used to calculate 95% confidence intervals around the costs (95% CI), based on the 2.5^th ^and 97.5^th ^percentiles. If cost data are distributed normally, t-tests will be used.

The incremental cost-effectiveness ratio (ICER) will be determined on the basis of incremental costs and effects of sex counselling compared to sexological treatment and a waiting-list group. The cost-effectiveness ratio will be stated in terms of costs per outcome rate (increase in sexual functioning, decrease of depressive symptoms) the cost-utility ratio will focus on the net cost per utility gained.

The robustness of the ICER will be checked by non-parametric bootstrapping. Bootstrap simulations will also be conducted in order to quantify the uncertainty around the ICER, yielding information about the joint distribution of cost and effect differences. The bootstrapped cost-effectiveness ratios will be subsequently plotted in a cost-effectiveness plane. The choice of treatment depends on the maximum amount of money that society is prepared to pay for a gain in effectiveness, which is called the ceiling ratio. Therefore, the bootstrapped ICERs will also be depicted in a cost-effectiveness acceptability curve showing the probability that sex counselling is cost-effective using a range of ceiling ratios. Additionally, to demonstrate the robustness of our base-case findings, multi-way sensitivity analyses will be performed [60].

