**Methods:**

In a randomised controlled trial we will compare (1) brief sex counselling with (2) intensive sexological treatment, and (3) delayed treatment (waiting list). Embedded in this RCT will be a trial-based economic evaluation, looking at the cost-effectiveness and cost-utility of brief sex counselling versus the two other interventions. Four hundred fifty adolescents (aged 18-25) with sexual problems will be recruited among the persons who visit the Public Health Service (PHS) and through various websites. After a screening procedure, eligible participants will be randomly allocated to one of the three intervention groups. Primary outcome measure of the clinical evaluation is the severity of sexual problems. Other outcomes include psychological distress, especially depression. The economic evaluation will be performed from a societal perspective. Costs will be assessed continuously by a retrospective questionnaire covering the last 3 month. All outcome assessments (including those for the economic evaluation) will take place via the internet at baseline, and at 3, 6, 9, and 12 months after baseline.

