### Sample size

In a repeated-measures analysis of the within-between-interaction effect, a sample size of 95 in each group has a power of 95% to detect an effect size of 0.41 using repeated-measures MANOVA with a 0.050 two-sided level of significance. In the absence of published controlled studies on professional care for young people with sexual problems, we set the desired effect size at d = 0.40, representing the central point of the range of effect sizes that are considered as 'medium size' [54]. N = 150 per condition is deemed necessary to guarantee the required number of respondents, in view of the expected non-response after inclusion and later attrition [55]. In a repeated-measures analysis of the within-subjects effect, a sample size of 86 in the treated group has a power of 95% to detect an effect size of 0.25 using a repeated-measures MANOVA with a 0.050 two-sided level of significance. The before mentioned N = 150 per condition is expected to guarantee the required number of participants.

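### The economic evaluation adjusts for baseline only if the groups look different; in a randomised trial adjustment should be unconditional, because baseline predicts follow-up

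*Protocol article*

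**What the plan says.** The rule is in the Analyses part of the protocol article, under Economic evaluation. It opens with a comparison of the groups: "A baseline analysis will be performed to examine the comparability of groups at baseline for both costs and outcomes". The next sentence makes adjustment depend on the outcome: "If necessary methods will be applied to control for differences in baseline". No criterion for necessity is given. A reference is cited for the methods.

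The cost comparison that the section names is unadjusted. If costs are skewed, "non-parametric bootstrapping will be used to test for statistical differences in costs between the intervention and control group"; under normality a t-test is named instead. For the ICER (the ratio of incremental cost to incremental effect), the section says that it "will be determined on the basis of incremental costs and effects of sex counselling compared to sexological treatment and a waiting-list group", and the cost-effectiveness plane and acceptability curve are built from the same bootstrap replicates.

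The baseline values will exist. The abstract states: "All outcome assessments (including those for the economic evaluation) will take place via the internet at baseline, and at 3, 6, 9, and 12 months". It adds that the cost questionnaire looks back over 3 months.

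For the clinical outcomes, the Clinical analyses section says that "difference scores for all outcome variables will be calculated and compared between the three intervention groups using MANOVA". The economic section does not say whether costs or utilities are analysed as change or with a baseline covariate. It does word the effects as an increase, a decrease or a gain.

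**The concern.** Allocation is random, so a baseline comparison between arms can only show chance. It says nothing about whether adjustment is worthwhile. That depends on how strongly the baseline value predicts the follow-up value within arms, which does not change with the observed imbalance.

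A rule that looks first and adjusts afterwards has three consequences:

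- When the trigger is not met, the prognostic information in baseline costs goes unused and the cost interval is wider than it need be.
- A chance imbalance just short of the trigger passes into the incremental cost, and into the incremental effect if that is also unadjusted.
- The estimator depends on the data, and with no criterion stated the choice can be made after the data are seen.

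The third objective of the study, cost-effectiveness, rests on the joint distribution of cost and effect differences. Avoidable spread there goes straight into the plane and the acceptability curve.

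**Working it through.** **The plan's own figure.** The article gives no precision or sample-size figure for the economic evaluation. The only one is clinical: "a sample size of 95 in each group has a power of 95% to detect an effect size of 0.41" (Sample size section). A plain two-group comparison with 95 per group and an effect of 0.41 has about 81% power. A repeated-measures MANOVA interaction with 3 groups, 5 measurements, total N = 3 × 95 = 285 and f = 0.41/2 = 0.205 gives 95.4% to 95.8%, so the stated figure is attainable. The conversion f = d/2 and the 5 measurements are assumptions. This figure does not bear on the present point; only the group sizes are borrowed from it.

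**Inputs.** Group sizes are 95 (analysable) and 150 (enrolled), from the Sample size section. The correlation ρ between baseline and follow-up is not given; 0.3, 0.5 and 0.7 are assumed. The trigger is not given either, so several are tried.

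**1. Unadjusted against baseline-adjusted.** SE ratio = 1/√(1 − ρ²).

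- ρ = 0.3: 1/√0.91 = 1.05
- ρ = 0.5: 1/√0.75 = 1.15
- ρ = 0.7: 1/√0.51 = 1.40

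At ρ = 0.5 adjustment is worth 1/0.75 = 1.33, that is, 33% more participants.

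**2. Change score against baseline-adjusted** (relevant if effects enter as change). SE ratio = √[2(1 − ρ)/(1 − ρ²)] = √[2/(1 + ρ)].

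- ρ = 0.3: √1.538 = 1.24
- ρ = 0.5: √1.333 = 1.15
- ρ = 0.7: √1.176 = 1.08

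**3. How often a trigger would lead to adjustment.** For one variable and one comparison, a baseline test at 5%, 10% or 20% leaves 95%, 90% or 80% of trials unadjusted. For a trigger on the standardised difference t, P(adjust) = 2[1 − Φ(t/√(2/n))]:

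| Trigger | n = 95, unadjusted | n = 150, unadjusted |
|---|---|---|
| t = 0.1 | 51% | 61% |
| t = 0.2 | 83% | 92% |

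If any one of two to four independent variables crossing 0.1 triggered adjustment of all, 62% to 93% of trials would adjust.

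**4. The two-stage rule simulated** (normal outcome, n = 95, adjust only if baseline p < 0.05; this reading is an assumption; 40,000 trials per setting).

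| ρ | Mean SE, two-stage | Mean SE, always adjusted | Type I error, two-stage | Type I error, always adjusted |
|---|---|---|---|---|
| 0.3 | 0.145 | 0.139 | 4.8% | 5.1% |
| 0.5 | 0.144 | 0.126 | 4.4% | 5.1% |
| 0.7 | 0.143 | 0.104 | 3.5% | 4.9% |

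The two-stage rule recovers little of the available precision and is slightly conservative.

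**5. Skewed costs** (lognormal, percentile bootstrap interval, same 5% trigger, 600 trials per setting). Ratio of the two-stage interval width to the always-adjusted width, n = 95:

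- linear ρ 0.22: 1.182/1.146 = 1.03
- linear ρ 0.39: 1.164/1.056 = 1.10
- linear ρ 0.60: 1.149/0.895 = 1.28
- linear ρ 0.72: 1.128/0.754 = 1.50

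At n = 150 the ratios are nearly the same (1.03, 1.09, 1.27, 1.48).

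**6. Imbalance that passes through.** At n = 95 a baseline difference above 0.2 SD occurs in 16.8% of trials, and a significant one in 5%, so about 12% have a difference above 0.2 SD that a 5% test misses. An unadjusted estimate then shifts on average by ρ times the imbalance: at ρ = 0.5 and exactly 0.2 SD, 0.5 × 0.2 = 0.10 SD.

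**The case against.** The strongest reply is that the size of the problem is unknown and may be small. No cost correlation is given. Part of the variation in cost comes from how many sessions are used, up to three or up to ten depending on the arm, and baseline cost may predict that poorly. This stands: at a correlation near 0.2 the gain is about 3% of interval width. The article is also condensed, so the trigger and the adjustment model may be set out elsewhere. That excuses missing detail, but the conditional rule itself is stated here.

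Three stronger readings are tempting, and the documents do not support them.

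- **A reader might infer that baseline data are thrown away in most trials.** No trigger is stated, so the proportion is an assumption. It holds for a 5% test on one variable, barely for a standardised difference of 0.1 at n = 95, and fails if any of several variables crossing 0.1 would trigger adjustment. For effects, the difference scores under Clinical analyses and the wording of the ICER outcomes suggest that baseline is probably used, as a change score.
- **A reader might infer a much larger loss for utilities**, by assuming that they are accumulated over all visits with baseline inside the sum. The article never states such an outcome; it speaks only of utilities and utility gained.
- **A reader might infer inflated false positives or systematic bias.** With a 5% baseline trigger the simulated type I error is at or below nominal, and randomisation leaves no systematic bias from omitting baseline.

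**Conclusion.** The point holds as a loss of precision and a data-dependent choice of estimator, clearest for costs. Observed baseline comparability is the wrong reason to adjust or not to adjust in a randomised trial, and unconditional adjustment is the better method at little cost.

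The size is uncertain because it rests on correlations that the article does not give. It could be negligible if baseline costs predict later costs weakly, and substantial if they predict them well. For effects analysed as change scores, the loss against regression is about 15% of the standard error at ρ = 0.5, smaller at higher correlations and larger at lower ones. This is a cheap improvement to the plan, not a flaw that invalidates the economic evaluation.

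**What to change.** Replace the conditional sentence in the Economic evaluation analysis section with an unconditional rule, for example:

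> Incremental costs will be adjusted for baseline 3-month costs, and incremental effects and utilities for the baseline value of the same measure, by regression fitted within every bootstrap replicate, with each participant's costs and effects resampled together. The adjusted differences will be used for the ICER, the cost-effectiveness plane and the acceptability curve, whatever the baseline comparison shows. Unadjusted results will be reported as a sensitivity analysis.

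Keep the baseline comparison as description only.

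The cost is a sentence or two of wording and a regression step in a bootstrap that is already planned. No new data are needed, since baseline costs and the SF-36 are collected. The one practical downside is that the Clinical analyses section names Excel for the bootstraps. A regression within each replicate is awkward there and may need other software.
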